#### 4.8 Analysis:

The patients will be divided into 3 age groups for age dependent analyses: 0-4 years, 5-14 years and above 14 years.

#### 4.9 Outcomes

##### Primary outcome:

Proportion of patients prescribed Coartem (out of all included patients)

##### Main secondary outcome

Proportion of patients with clinical recovery by day 3 and 7, respectively, out of all included patients.

##### Other Secondary outcomes:

###### In all patients

- Proportion of patients prescribed *antibiotics* and/or antipyretics (on day 7 patients will be asked if they have been prescribed any other drugs than Coartem from CHW)
- Proportion of patients presenting to CHW within 24 hours after onset of fever (compared to those presenting >24 hours)
- Cost of diagnosis and treatment(s)
- Sensitivity and specificity of RDT vs. microscopy
- Reasons for prescribing Coartem despite negative RDT

- Proportion with new episode of malaria (BS confirmed) within 28 days
- Proportion with Coartem tablets remaining day 3

#### In children <5 (Coartem – “CCC” study)

- Proportion with new clinical episode of malaria up to day 42
- Proportion with parasitemia/recrudescence (PCR adjusted) day 7 to 42
- Proportion with lumefantrine concentrations below 280 µg/L on day 7±2

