## 2. Hypotheses

**Hypothesis 1:** RDT used by CHWs for the identification of non-severe clinical malaria will reduce use of Coartem by 30 % without affecting health outcome.

**Hypothesis 2:** The effectiveness/parasitological cure of Coartem for the treatment of uncomplicated malaria at community level is above 90 % as assessed in a 42 day follow up in children <5 years old.

**Hypothesis 3:** The use of RDT and Coartem is well perceived by the community and will enhance health seeking behaviour.

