### 3.3 Specific objectives

1. To determine the proportion of children and adults who receive malaria treatment (ACT) from CHWs within 24 hours of onset of symptoms vs. later.
2. To determine the ability of CHWs to correctly assess the presence or absence of malaria using RDT's.
3. To explore reasons for potentially treating RDT negative patients with Coartem.
4. To assess the predictive value of erratic fever ("homa ya vipindi") as a clinical tool to differentiate malaria from other causes for fever.
5. To assess health status of patients in all age groups days **3 and 7** (active follow up) and up to day 28 (passive follow up) after contact with CHW.
6. To assess management cost of clinical episodes of fever by CHWs with or without RDT's.
7. To study PCR adjusted antimalarial effectiveness of Coartem treatment in children <5 years with uncomplicated malaria by trained CHWs (with or without the diagnostic support of RDT) up to day 42.

8. To explore compliance to Coartem regimen **in all age groups.**
9. To explore the attitudes of CHWs and patients towards RDT's and Coartem at community level.

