#### **4.16 Concomitant drug therapy**

Substance and day of administration for any antibiotics or other treatments (including traditional remedies) taken during the first 7 days will be recorded in the CRF on day 7.

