## **6.3 Teaching period (20th - 24th February 2006)**

1. Training of the chosen CHWs (and Clinical officers) for one week.
2. The following messages will be emphasised in IEC:
  - i. Prompt recognition of malaria symptoms.
  - ii. Prompt treatment and compliance with study drugs.
  - iii. Importance of fat intake with ACT
  - iv. Prompt recognition of non-response to treatment and the need to promptly seek treatment from a trained health facility worker.

- v. Prompt recognition of severe disease and IMCI danger signs in children and prompt referral to appropriate level.
- vi. The need to comply with referral for severe disease and non-response to initial treatment
- vii. Practical skills in performing tests of blood and storage of samples

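### The under-five PCR-adjusted outcome starts on day 7, so a Coartem failure on days 1-6 that is treated elsewhere and clear by day 7 is not counted against the 90 % cure hypothesis

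*Protocol*

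**What the plan says.** Section 2, Hypothesis 2, states that the effectiveness or parasitological cure of Coartem at community level "is above 90 % as assessed in a 42 day follow up in children <5 years old". Section 3.3, objective 7, is "To study PCR adjusted antimalarial effectiveness of Coartem treatment in children <5 years", up to day 42. Neither has a start day later than treatment.

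Section 4.9 lists two outcomes for under-fives that concern treatment failure:
- "Proportion with parasitemia/recrudescence (PCR adjusted) day 7 to 42"
- "Proportion with new clinical episode of malaria up to day 42"

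The first is the only PCR-adjusted outcome. It has no stated denominator and no rule for a child treated elsewhere before day 7.

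In section 4.18 B, day 3 has a questionnaire and a lumefantrine level, and the first scheduled smear after Day 0 is on day 7. Section 4.25 adds a slide at follow-up visits when there is fever. Section 6.3 lists this among the messages to be emphasised: "Prompt recognition of non-response to treatment and the need to promptly seek treatment from a trained health facility worker". Under section 4.16, antibiotics and other treatments "taken during the first 7 days will be recorded in the CRF on day 7". Sections 4.14 and 4.18 refer under-five follow-up to a separate CCC protocol.

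**The concern.** The hypothesis covers the whole course from treatment to day 42, but the outcome that measures it begins a week in. The study's own messages send non-responders to a facility. Treatment there may clear the parasites before the first scheduled smear, and the child then has nothing to record inside the day 7 to 42 window.

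Early failures are the clearest evidence against a drug, and the hypothesis is judged against a fixed 90 % line. Leaving them out can move the estimate in one direction only, in favour of Coartem.

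**Working it through.** No figure in the protocol depends on the day 7 start, so there is none to reproduce. The check is a trace through the outcomes, followed by the size under stated assumptions.

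**Step 1. Trace one child.** The child is infected on Day 0, treated with Coartem, worsens on day 3, is given another antimalarial at a facility and is smear-negative on day 7 and after.
- PCR-adjusted outcome, days 7-42: no event. A positive slide on day 3, if one was taken for fever, still lies outside the window.
- New clinical episode up to day 42: there is no lower time bound, but a persisting Day-0 illness is not plainly a new episode.
- Clinical recovery by days 3 and 7: may show non-recovery on day 3. Its denominator is all included patients of any age, infection status or treatment, so it does not feed a cure proportion.
- Treatment record in 4.16: captures the other drug, but no outcome uses it.

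A child still parasitaemic on day 7 is counted. The gap concerns only those who are clear by then.

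**Step 2. Direction.** Let e be the share failing on days 1-6 and clear by day 7, and f the share with PCR-adjusted failure on days 7-42. Neither is in the protocol.
- True cure = 1 − e − f.
- Early failures kept as non-failures: 1 − f, too high by e.
- Early failures dropped: 1 − f/(1 − e), too high by e(1 − e − f)/(1 − e).

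Both errors are positive whenever e > 0 (and some children are cured) and zero at e = 0. With f assumed to be 5 %:

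| e | True cure | Kept as non-failures | Dropped |
|---|---|---|---|
| 0 % | 95.0 % | 95.0 % | 95.0 % |
| 1 % | 94.0 % | 95.0 % | 94.9 % |
| 2 % | 93.0 % | 95.0 % | 94.9 % |
| 4 % | 91.0 % | 95.0 % | 94.8 % |
| 5 % | 90.0 % | 95.0 % | 94.7 % |

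**Step 3. Size at n = 240** (the minimum number of infected under-fives in section 4.10). One child is 1/240 = 0.42 points. Early failure of 1 %, 2 % and 4 % is 2.4, 4.8 and 9.6 children, or about 1, 2 and 4 points. As an illustration chosen to lie near the threshold, take 213 cured, 22 late failures and 5 early failures. True cure is 213/240 = 88.8 %. Kept as non-failures, the early failures give 218/240 = 90.8 %. Dropped, they give 213/235 = 90.6 %.

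**Step 4. Effect on the 90 % decision.** The protocol names no test, so I assume an exact one-sided binomial test at 0.025. With n = 240 it needs 226/240 (94.2 %), and its actual level is 1.5 %. If true cure is exactly 90 %, the chance of wrongly concluding that it exceeds 90 % is:

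| e | Kept as non-failures | Dropped |
|---|---|---|
| 1 % | 4.8 % | 4.8 % |
| 2 % | 12.9 % | 13.0 % |
| 3 % | 28.9 % | 28.7 % |
| 5 % | 77.7 % | 68.4 % |

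**The case against.** The strongest reply is that section 4.9 only lists outcomes, and that the under-five sub-study is handed to a separate protocol, not shown, which may define early failure and the denominator. That is a fair limit. But the hypothesis and the day 7 window are both stated in this document. If the CCC protocol counts early failures, the two texts differ and need aligning; if it does not, the gap is real.

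A reader might infer that such a child is scored as cured and that the result is overstated. The protocol supports neither. It writes no scoring rule, so failure, exclusion and censoring all remain open, and the early-failure rate may be near zero. What does stand is that keeping these children as non-failures and dropping them err in the same direction.

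It can also be said that a child treated elsewhere need not be clear on day 7. Section 4.25 says facilities will not provide ACT during the study, and section 1.1 reports resistance to sulfadoxine-pyrimethamine of 15 % in many areas and up to 34 % in one. Some of these children will therefore be counted, which reduces e but does not make it zero.

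Starting at day 7 also fits the smear schedule. That explains the choice, but the hypothesis is still worded for the full 42 days.

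Finally, counting every referral or admission as drug failure would bring its own bias, because an unrelated illness would count against Coartem. This is right, and it limits the fix.

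**Conclusion.** The concern holds as a mismatch between the hypothesis and its outcome window. A failure on days 1-6 that is treated elsewhere and clear by day 7 is not counted as worded, and no other outcome brings it into the cure proportion. Cure against the 90 % threshold can then be overstated.

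The size rests entirely on an assumed early-failure rate: nothing at 0 %, and about 1 to 4 points at 1 to 4 %. It also takes the stated minimum of 240 as the denominator. This bears on one secondary hypothesis and leaves the primary outcome, Coartem prescription, untouched. It should be corrected before the cure result is read against 90 %.

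**What to change.** In section 4.9, define the failure outcome for Hypothesis 2 in children with Day-0 parasitaemia who were treated with Coartem, and start its window after Day 0. Count as failure:
- another antimalarial taken for persisting or worsening illness on days 1-6, from the 4.16 record and with the slide result where one was taken;
- malaria death;
- PCR-adjusted parasitaemia on days 7-42.

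Keep the early failures in the denominator, report them on their own line, and add a sensitivity analysis that censors them. Report referral or admission without parasitological evidence separately, and do not count it automatically as failure. Make the wording match the CCC protocol.

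This classifies outcomes only and leaves clinical management as it is. The cost is a change of wording, an extra table line and one sensitivity analysis. Other treatments are already recorded, but the reason for taking them, referral, admission and death may need an added item on the form. The cure estimate may be slightly less favourable, and some precautionary treatments may be counted as failures.

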#### **Tertiary outcomes**

- Attitudes of CHWs and patients towards RDT
- Attitudes of patients to Coartem regimen

#### **4.10 Study Power/sample size estimation**

Below is a tentative (very arbitrary) assumption of “fever” and “malaria episode” incidences per month in a population of 1000 people on which to build sample size calculation (assuming 6 months of wet and dry seasons, respectively).

|                            | n    | Wet season |         | Dry season |         | Yearly fever |
|----------------------------|------|------------|---------|------------|---------|--------------|
|                            |      | Fever      | Malaria | Fever      | Malaria |              |
| <5                         | 200  | 100        | 50      | 60         | 10      | 960          |
| 6-15                       | 300  | 45         | 15      | 30         | 5       | 450          |
| ≥15                        | 500  | 50         | 10      | 50         | 5       | 600          |
| Total                      | 1000 | 195        | 75      | 140        | 20      | 1710         |
| Attendance to CHW
(80%) | 800  | 156        | 60      | 112        | 16      | 1368         |

The sample size/population/number of CHWs suggested by the settled study design:

Population size: 8,000

Number of villages: 7

Number of CHWs: 22

Time period: 16 weeks of patient recruitment + 1 remaining week follow up

Estimated no. of fever patients: Minimum 3,200

Number of malaria infected <5s for Coartem study: minimum 240

The number to be treated with Coartem with/without RDT for 4 months in 8000 people will tentatively be =

| Treatment                                                              | <5   | 6-14 | ≥15  | Total |
|------------------------------------------------------------------------|------|------|------|-------|
| With RDT (assuming 70%, 50% & 30% positivity for respective age group) | 1436 | 481  | 384  | 2302  |
| Without RDT (90% for all ages)                                         | 1845 | 865  | 1153 | 3863  |

The available sample size is given in this study. The aim of the following power calculation is to check the influence on the power of potential clustering within the design. Clustering can be assumed on two levels, on the village level and on the CHW level. The latter can be assumed to be potentially the most severe in this study since the outcome of the intervention will be heavily dependent on the behaviour and engagement of the CHWs. In the sequel calculations on village level is omitted potentially resulting in non-conservative results.

The study should be able to detect a reduction of 10 percentage units in Coartem prescriptions in each group when using RDT, i.e. from 80% to 70%, with a power of 80% and a significance level of 5%. Assuming independent data a sample size of 314 fever patients attending the CHW per study group is required which will be met for each age group during the study period. However, under assumption of potential clustering within the 20 CHWs the influence on the power have to be derived. Here, based on the available number of fever cases, table X, the largest possible ICC (Intra Cluster Coefficient) where the power requirements still are fulfilled have been calculated in Table X+1.

Table X. Total sample size per study group (+/- RDT) during study period of 16 weeks in 7 villages with in total 8000 inhabitants.

|                               | <5   | 6-14 | ≥15 | Total |
|-------------------------------|------|------|-----|-------|
| Total “fever”                 | 1280 | 600  | 800 | 2680  |
| Total “malaria”               | 480  | 160  | 120 | 760   |
| Fever cases seen by CHW (80%) | 1024 | 480  | 640 | 2144  |

Table X+1. Maximum ICC under the power requirements and given sample sizes for fever cases seen by CHW.

|                               | <5    | 6-14  | $\geq 15$ | Total |
|-------------------------------|-------|-------|-----------|-------|
| Fever cases seen by CHW (80%) | 1024  | 480   | 640       | 2144  |
| Number of cases per CHW       | 51    | 24    | 32        | 107   |
| Maximum ICC                   | 0.045 | 0.023 | 0.033     | 0.055 |

From Table X+1 it can be seen that the study design fulfils the power requirements for  $ICC < 0.023$  for all age groups. For the total cohort and for children under five years an  $ICC < 0.045$ , respectively, are possible, which can be regarded as satisfactory since the ICCs in community health setting tend to be small.

It also notable that the study design is paired on a group level, i.e. each CHW is alternately using +/- RDT on weekly basis. This partly controls for the between-CHW variation which reduces the needed sample size compared to ordinary pretest-posttest control group design. The needed sample sizes above can be multiplied with  $(1-p)$  where  $0 < p < 1$  is the correlation coefficient for random pairs of patients from +/- RDT groups treated by the same CHW. Assuming  $p=0.10$  will then decrease the needed number sample size to 90% out of the given figures.

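### Section 4.10 checks power under clustering only at Table X's 4,288 attended fevers; the ICC < 0.023 limit for all age groups is not checked at the stated minimum of 3,200, and Table X counts four months as 16 weeks

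*Protocol*

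**What the plan says.** All of the figures below are in Protocol section 4.10 unless stated otherwise.

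- The list for the settled design (8,000 people, 7 villages, 22 CHWs, 16 weeks of recruitment) has the line "Estimated no. of fever patients: Minimum 3,200".
- The target is a fall in Coartem prescription from 80% to 70% with 80% power at the 5% level. "Assuming independent data a sample size of 314 fever patients attending the CHW per study group is required". The plan expects every age group to reach this number.
- The clustering check is made "under assumption of potential clustering within the 20 CHWs", using the counts in Table X.
- Table X is captioned "Total sample size per study group (+/- RDT) during study period of 16 weeks in 7 villages with in total 8000 inhabitants". Its attended fevers per group are 1,024 (<5), 480 (6-14) and 640 (15 and over), 2,144 in total.
- Table X+1 turns these into maximum ICCs of 0.045, 0.023, 0.033 and 0.055.
- The conclusion, drawn for every age group at an ICC below 0.023, opens with "From Table X+1 it can be seen that the study design fulfils the power requirements for". A value below 0.045 is called possible for children under five and for the total cohort.
- The closing paragraph adds that within-CHW pairing allows the needed sizes to be multiplied by 0.90 if the correlation is 0.10.

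Section 4.25 says that the crossover runs for 16 weeks, or for less if the sample size is reached.

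**The concern.** Table X is per study group, so the check uses 2 x 2,144 = 4,288 attended fevers. That is 34% above the minimum in the same section (4,288 / 3,200 = 1.34). The tolerable ICC depends steeply on the count when the count is not far above 314, which is the position of ages 6-14, the group that sets the limit for all age groups. A limit that is valid at 480 per group need not hold at the number the plan gives as its floor.

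The 80% requirement is set for each age group, and section 4.8 plans analyses by age. The early-stop wording in section 4.25 refers to a sample size, but section 4.10 offers both 3,200 and 4,288. Stopping at the lower figure would leave the 6-14 comparison below the power that the protocol reports for ICC 0.023, and an imprecise result there could be read as coming from an adequately powered comparison.

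**Working it through.** **1. Reproduce the 314.** Inputs from section 4.10: 0.80 vs 0.70, 5% (sidedness is not stated; two-sided reproduces the figure), 80% power.

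n = [1.96 x sqrt(2 x 0.75 x 0.25) + 0.8416 x sqrt(0.16 + 0.21)]² / 0.10² = 293.2, so 294. With the continuity correction, n/4 x [1 + sqrt(1 + 4/(n x 0.10))]² = 312.8, so 313. The plan's 314 is the continuity-corrected size.

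**2. Reproduce Table X+1.** Maximum ICC = (N/314 - 1) / (N/20 - 1), with N the attended fevers per group.

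- <5: (1024/314 - 1) / (51.2 - 1) = 0.045
- 6-14: (480/314 - 1) / (24 - 1) = 0.023
- 15 and over: (640/314 - 1) / (32 - 1) = 0.0335
- Total: (2144/314 - 1) / (107.2 - 1) = 0.055

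These agree with the printed limits apart from rounding, so the table follows correctly from Table X.

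**3. Check the time base of Table X.** For ages 6-14 the mean monthly fever count per 1,000 people is (45 + 30)/2 = 37.5. Then 37.5 x 8 x 4 months / 2 groups = 600, and x 0.8 = 480, as printed. Sixteen weeks is 112/30.44 = 3.68 months, so each entry is too high by 4/3.68 = 1.087, about 9%. At 3.68 months the attended counts are 942, 442 and 589 per group. The 6-14 limit becomes (441.6/314 - 1) / (22.08 - 1) = 0.019. Power at ICC 0.023 is 78% with the continuity correction and 81% without it.

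**4. Repeat the check at 3,200.** Assumption: 1,600 per group, split by age as in Table X (factor 3200/4288 = 0.746), because the protocol gives no age split for 3,200.

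| Age group | N per group | Printed limit | Limit, 20 CHWs | Limit, 22 CHWs |
|---|---|---|---|---|
| <5 | 764 | 0.045 | 0.0385 | 0.0425 |
| 6-14 | 358 | 0.023 | 0.0083 | 0.0092 |
| 15 and over | 478 | 0.033 | 0.0228 | 0.0252 |
| Total | 1,600 | 0.055 | 0.0518 | 0.0571 |

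**5. Power for ages 6-14 at ICC 0.023 and 3,200.** With 20 CHWs, m = 358.2/20 = 17.9, the design effect is 1 + 16.9 x 0.023 = 1.39, and the effective n is 358.2/1.39 = 258. Power is 71% with the correction that yields 314 and 75% without it. With 22 CHWs the effective n is 265 and power is 73-76%.

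**6. Add the plan's 10% pairing credit.** The needed size is 0.9 x 314 = 282.6. The 6-14 limit at 3,200 is (358.2/282.6 - 1) / (17.9 - 1) = 0.0158 with 20 CHWs and 0.0175 with 22. Power at ICC 0.023 is 76-79% and 77-80% respectively.

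**7. Sensitivity to the age split.** If 3,200 is a dry-season floor (an inference: 112 x 8 x 3.68 = 3,297 attended fevers), ages 6-14 would have 30 x 0.8 x 8 x 3.68 / 2 = 353 per group. The limit is then 0.0075 and power 71-74%, so the result does not hinge on Table X's split.

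**The case against.** A reader might infer that 3,200 and 4,288 contradict each other. They do not: a minimum is compatible with a larger expected number, and recruitment is meant to span both seasons, which supports a wet/dry average for planning. The Coartem treatment table also implies about 4,290 attended fevers (for example 1,845/0.90 = 2,050 under five, against 2 x 1,024 = 2,048), so 3,200 is the odd figure in the section and may be the one to correct.

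A reader might also infer that the power claim is made without condition. It is tied explicitly to Table X and Table X+1, and Table X+1 already shows 480 next to 0.023. What stands is that the check was not made at the minimum.

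The limit of 0.008 leaves out the pairing credit, which the protocol describes. With the credit the limit about doubles. Moreover, 1 + (m - 1) x ICC is a parallel-cluster design effect, and a within-CHW crossover may do better, although the protocol gives no correlation beyond the illustrative 0.10. The two limits should therefore be shown together.

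Finally, the practical loss is modest. An effective n of 258 gives about 80% power for 11 points instead of 10. If Hypothesis 1 means a 30% relative reduction, 80% to 56% has power above 99.9% at that size. The monthly incidences are labelled as very arbitrary, and the section itself speaks of 4 months, so the 9% slip is small beside their uncertainty. These points limit the consequence, but they leave the stated ICC limit uncorrected.

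**Conclusion.** The concern holds as a defect in a stated power property. Under the plan's own formula (314, 20 CHWs), the 6-14 limit is about 0.019 once Table X is put on 16 weeks. At the stated minimum it is about 0.008 (0.0158 to 0.0175 with the pairing credit), against the printed 0.023. Only the combination of 22 CHWs, no continuity correction and the pairing credit brings it back to 0.0231, and that sets aside the plan's own 314 and 20.

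At 3,200 the 0.045 statement also fails for children under five without the credit (limit about 0.039; with the credit 0.0458). Ages 15 and over are borderline at 0.0228.

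It would be wrong to conclude that the primary comparison in all patients is underpowered: the total-cohort limit is still 0.052, and power at ICC 0.023 is 97%. The size of the shortfall rests on equal groups and an assumed age split at 3,200.

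**What to change.** In section 4.10:

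- State how 3,200 relates to 4,288, or correct whichever figure is wrong, and say which one is the target for the early-stop wording in section 4.25.
- Recompute Table X at 16 weeks (3.68 months), and Table X+1 with one CHW count, since the section uses both 20 and 22.
- Add a row to Table X+1 at the stated minimum, with and without the pairing credit.
- Restate the all-age-groups claim: ICC < 0.023 holds at about 480 attended fevers per study group in ages 6-14, with the lower limit given for the minimum.

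The cost is wording and a recalculated table. No extra enrolment is needed. The downside is a less favourable stated ICC limit for ages 6-14, which may have to be described as having less than 80% power at minimum recruitment.
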